## 3. Methods

This will be a multicentric randomized controlled trial with blinded outcome assessments coordinated by the Department of Mental and Physical Health and Preventive Medicine at the University of Campania Luigi Vanvitelli, and it will be conducted in 24 Italian outpatient clinics.

Eligible patients and their families will be identified by their treating clinicians and referred to the specialized staff to be included in the study. After acceptance, an informed consent form will be signed and an appointment for baseline assessments will be made. Consent can be withdrawn at any time by both patients and their relatives. Patients will be randomly assigned in a 1:1 ratio to the experimental group or the control group. The randomization will be stratified according to the recruiting center and each patient’s age, sex, and educational level. The procedure will be implemented in the coordinating center using specific statistical software. The researchers and statisticians involved in the patients’ assessments will be blinded each patient’s allocation. The mental health professionals providing the interventions will not be blinded to the patients’ allocations.

Patients referred to the outpatient units of participating mental health centers will be invited to participate in the study if they meet the following inclusion criteria: (1) diagnosed with MDD according to the Diagnostic and Statistical Manual of Mental Disorders, Fifth Edition (DSM-5); (2) between 18 and 65 years of age; (3) admitted to the local mental health center for at least 6 months, with at least one access per month; (4) ability to provide written informed consent; (5) cohabitation with at least one family member.

Patients with intellectual disabilities will not be eligible, and neither will patients who experience a clinically relevant worsening of psychiatric symptoms (i.e., requiring a substantial change in the therapeutic dosage of psychiatric medications or access to emergency care or hospitalization) during the two months before recruitment. Patients with comorbid physical illnesses will not be excluded from the study unless the physical condition is so severe and disabling as to require intensive medical care. All recruited patients will continue to receive the treatments usually provided in their centers, which include regular outpatient psychiatric assessments, pharmacological treatments, and management of the side effects of medications. All patients will receive an adequate pharmacological treatment according to the NICE [51] guidelines for the whole duration of the study.

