## Abstract

This study aims to assess the efficacy of a psychoeducational family intervention (PFI) to reduce the severity of depressive symptoms and to improve psychosocial functioning and to increase social contacts in a sample of patients with major depressive disorder (MDD). The degree to which PFI will reduce patients’ relapses, hospitalizations, and self-stigmatization and will improve their quality of life will also be assessed. Other secondary outcomes include the improvement of relatives’ coping strategies, family burden, expressed emotions and quality of life. This non-profit, unfunded, national, multicentric randomized controlled trial with blinded outcome assessments will be carried out in 24 Italian university outpatient units. Families will be assessed at baseline and at 6, 12, and 24 months post-randomization. Our working hypothesis is that the PFIs will reduce the patients’ severity of depressive symptoms, their relapses, and their hospitalizations, and that they will improve their psychosocial functioning and quality of life. We expect these results to be maintained after 12 and 24 months, albeit with a reduction in magnitude. The sample will consist of 384 patients randomized at a 1:1 ratio and stratified according to center, age, gender, and educational level.

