## 9. Statistical Analyses

### 9.1. Power Analysis

The sample size was estimated with respect to the measurement of the main outcomes of the study, and the measure that required the largest sample size (HAM-D) was taken as the reference. Specifically, a sample size sufficient to reduce the total HAM-D score by 10%, with a two-tailed probability of 0.05% and a power of 90%, was estimated. The multicenter design of the study required an adjustment of the sample size estimate in accordance with the value of the intracluster correlation coefficient, set at 0.030, and the coefficient of variation of cluster sizes, set at 0.400. The estimated sample size is 176 patients, 88 for each arm. Based on previous studies conducted with similar patient populations, a dropout rate of 15% is expected. Therefore, it will be necessary to recruit 384 families, 192 for each arm. Each participating center is expected to recruit 16 families (8 for each arm).

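### Stratifying 384 families by centre, age, sex and education gives at least 192 cells averaging two families or fewer, so balance within centres is not assured if the cells are crossed and blocked

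*Protocol article*

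**What the plan says.** Section 3 (Methods) gives the allocation rule: "Patients will be randomly assigned in a 1:1 ratio to the experimental group or the control group", and "The randomization will be stratified according to the recruiting center and each" patient's age, sex and educational level. The Abstract repeats it: "The sample will consist of 384 patients randomized at a 1:1 ratio and stratified according to center, age, gender, and educational level". Section 3 also says of the trial that "it will be conducted in 24 Italian outpatient clinics".

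Section 9.1 (Power Analysis) states that "it will be necessary to recruit 384 families, 192 for each arm", and that "Each participating center is expected to recruit 16 families (8 for each arm"). The same section assumes a coefficient of variation of centre size of 0.400.

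Section 3 places the procedure at the coordinating centre, run with statistical software. The article does not say how many bands age and education have, whether blocks are used and of what size, or whether the factors are crossed or balanced on their margins. The covariates that Section 9.2 lists for the generalized estimating equations include age and gender but neither centre nor educational level.

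**The concern.** Blocked stratification balances the arms only where blocks are filled. Each centre expects 16 families. Cutting those 16 into eight or more cells leaves most cells with very few families, and unfilled blocks then add up to imbalance within the centre and across the trial. Adding three patient factors can therefore weaken balance on centre. The plan treats centre as influential, since Section 9.1 adjusts the sample size for an intracluster correlation of 0.030.

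Balance within centres also matters in practice. Section 5 trains two professionals per centre in delivering the interventions, so a centre that ends 11:5 differs from the expected 8 per arm in workload as well as in information. For centre and educational level, the article names randomisation as a control but does not list them as model covariates.

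**Working it through.** **Inputs from the article:** 24 centres, 1:1 allocation and four factors (Section 3); 384 families, 16 per centre, 8 per arm (Section 9.1).

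**Assumptions:** at least two bands of age and two of education; fully crossed cells with permuted blocks; exactly 16 families per centre; each cell within a centre equally likely.

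**1. The plan's own figures.** 24 x 16 = 384 and 24 x 8 = 192 per arm. They agree.

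**2. Number of cells.**
- Two levels each: 24 x 2 x 2 x 2 = 192; 384/192 = 2.0 families per cell. This is the minimum for a crossed scheme.
- Three education levels: 24 x 2 x 2 x 3 = 288; 384/288 = 1.3.
- Three levels of age and of education: 24 x 3 x 2 x 3 = 432; 384/432 = 0.9.

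**3. Spread over cells.** With eight cells per centre, a cell's count is binomial (16, 1/8). Expected empty cells per centre: 8 x (7/8)^16 = 0.94. Expected cells with one family: 8 x 16 x (1/8) x (7/8)^15 = 2.16. So two families is the mean, not the count in each cell.

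**4. Imbalance left over.** Only the last, unfilled block of a cell contributes. With r families in an unfilled block of size b, the arm difference d has mean 0 and E(d²) = r(b − r)/(b − 1).
- Blocks of 2: the count is odd with probability (1 − 0.75^16)/2 = 0.495. Variance per centre 8 x 0.495 = 3.96; trial-wide SD √(24 x 3.96) = 9.7.
- Blocks of 4: r is 1 or 3 with probability 0.495 (E(d²) = 1), and 2 with probability 0.297 (E(d²) = 4/3). Per cell 0.495 + 0.396 = 0.891; per centre 7.13; trial-wide SD √(24 x 7.13) = 13.1.
- Simple randomisation: variance per centre 16; trial-wide SD √384 = 19.6.

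Summing the exact distribution of d over all ways that 16 families can fall into the cells gives:

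| Scheme | Centres 8:8 | Centres 10:6 or worse | Trial-wide SD of arm difference | Imbalance variance removed |
|---|---|---|---|---|
| 192 cells, blocks of 2 | 39% | 12% | 9.7 | 75% |
| 192 cells, blocks of 4 | 30% | 25% | 13.1 | 55% |
| 192 cells, blocks of 6 | 25% | 34% | 15.5 | 37% |
| 432 cells, blocks of 2 | 29% | 27% | 13.5 | 52% |
| 432 cells, blocks of 4 | 23% | 37% | 16.7 | 27% |
| 432 cells, blocks of 6 | 22% | 41% | 17.9 | 17% |
| Simple randomisation | 20% | 45% | 19.6 | 0% |

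A simulation of 600 trials agrees to within sampling error (8:8 at 192 cells: 39%, 30% and 26%). Unequal cells (assumed splits of 40/60 for age, 65/35 for sex, 60/40 for education) change little: 39%, 32% and 26%.

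**5. Comparison.** Centre-only fixed blocks of 4 or 8 give 8:8 in every centre that recruits exactly 16. Randomly varied blocks of 2, 4 or 6 do not guarantee this, but after 16 allocations the unfilled block holds 0, 2 or 4 families, so the difference is at most 2, that is 9:7.

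**6. Cost in precision.** Relative efficiency for a trial-wide difference D is 1 − (D/384)²: a loss of 0.3% for D = 20 and 1.1% for D = 40. If centre is fitted as a fixed effect, the loss against perfectly balanced centres is about E(d²)/16²: 3.96/256 = 1.5% for blocks of 2, 7.13/256 = 2.8% for blocks of 4, and 10.05/256 = 3.9% for blocks of 6, at 192 cells.

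**The case against.** The strongest reply is that the mechanism is not stated. The article says only that allocation is stratified and run centrally with software. That is compatible with minimisation, which does not have this problem, and a condensed article may leave the detail to the full protocol. This stands: the point is conditional on crossed, blocked cells, and the missing detail is not itself the finding.

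A reader might infer that stratification largely stops working. The figures do not support that at the minimum: with 192 cells, blocks of 2 or 4 still remove about 75% or 55% of the imbalance variance. Only many categories combined with large blocks come close to simple randomisation, and the article states neither.

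A reader might also infer that the stated 8 per arm per centre will not be delivered. Section 9.1 words it as an expectation, and its coefficient of variation of 0.400 shows that the authors do not assume 16 families everywhere. Under 1:1 allocation, 8 remains the mean in a 16-family centre, and 88% (blocks of 2) or 75% (blocks of 4) of such centres would be 9:7 or better.

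It is also true that chance imbalance causes no bias, that the precision loss is small, and that the model already lists age and gender.

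The count of cells still stands, because factors, centres and sample size are all stated. Very small blocks are not a clean escape: with blocks of 2 the second allocation in a cell follows from the first, while Section 3 leaves those who deliver the interventions unblinded and has treating clinicians identify families.

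**Conclusion.** Upheld as a minor, conditional point. The stated factors give at least 192 cells averaging two families or fewer. If these are crossed and blocked, balance within centres is not assured: about 40%, 30% or 25% of 16-family centres end exactly 8:8 with blocks of 2, 4 or 6, against 20% with simple randomisation. Stratification remains useful at 192 cells and fades as categories or block size grow.

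The percentages rest on 16 families per centre, near-even cells and permuted blocks, none of which the article fixes. The consequence is lost balance, with a precision loss of about 1% for a trial-wide difference of 40 families and roughly 1.5% to 4% at 192 cells if centre is a fixed effect. The treatment estimate is not biased by it.

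**What to change.** Before the first family is randomised, choose one of two set-ups and name it in the protocol:

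- Minimisation with a random element over the same four factors, run by the coordinating centre. This keeps all four factors and avoids sparse cells.
- Stratification by centre alone with randomly varied blocks. This brings 16-family centres close to 8:8 without guaranteeing it, and leaves age, sex and education to covariate adjustment. Blocks within a small centre are easier to guess, so block sizes should be withheld from the sites.

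In either case, put every randomisation factor in the primary generalized estimating equations, which means adding centre and educational level to the list in Section 9.2.

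The cost is a change in the central set-up and, for minimisation, some programming and testing. Adding the covariates costs nothing in data, since both are recorded. If minimisation is already intended, one sentence saying so settles the allocation part.

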## 4. Interventions

The experimental intervention will consist of the Falloon psychoeducational family intervention, which was developed for the treatment of schizophrenia [52], but which we have adapted for the treatment of major depression. The experimental intervention will be administered individually to each recruited family and consist of the following six phases: (1) engagement of the family unit; (2) individual assessment; (3) family assessment; (4) informative sessions; (5) communication skills sessions; and (6) problem-solving skills sessions.

The informative sessions will deal with the following issues: (1) clinical characteristics of MDD, symptoms, prognosis, risk and protective factors; (2) available pharmacological and non-pharmacological treatments for MDD, indications, side effects and strategies to cope with them, treatment duration, risk factors for relapse, and effects related to abrupt cessation of the therapy; and (3) early warning signs. A specific informative session on suicide risk has been developed, and this will be administered only to patients who report suicidal ideation during the intervention or who have a history of suicide attempts or ideation.

The sessions will take place three times a month for a period ranging from 4 to 6 months (about 18 sessions in total). The number of sessions, as well as their frequency, may vary depending on each patient’s clinical situation. Sessions will have an average duration of 60–90 min and will require the active participation of all family members, including the patient. Between sessions, participants will be invited to organize “family meetings” to discuss the topics covered during the previous meeting, progress made, and problems encountered in implementing changes. Each meeting will ideally be divided into three phases: a first phase dedicated to clarifications and questions regarding the topics previously discussed, a second phase focused on the main topic of the meeting (the so-called “teaching phase”), and a final phase in which the key points addressed during the session are summarized and in which “homework” is assigned.

The control group will receive an educational five-session intervention, administered every 7–10 days, on the following topics: healthy lifestyle (diet and nutrition), stress management, regulation of circadian rhythms, and the management of medication side effects. The control group sessions will last 60–90 min and will be as interactive as possible. At the end of each session, participants will receive leaflets and cards summarizing the key-points addressed during the session.

Treatment fidelity among the different centers will be secured by the development of manuals for both interventions and by continuous supervision, either on site or via phone calls.

The interventions will be discontinued under the following circumstances: (1) if patients or their relatives are unable to attend more than five consecutive psychoeducational sessions; (2) if patients are hospitalized or experience any affective relapse during the intervention; or (3) if patients or relatives withdraw their consent.

## 5. Training of Mental Health Professionals

Two mental health professionals per center (at least one being a psychiatrist) will participate in a four-day training course on the use of the interventions. During the training, a manual explaining how to conduct the experimental intervention will be provided to participants, and several role-play sessions will be organized. An additional training course on the use of assessment instruments will be organized, and this will include the following phases: (a) presentation of the assessment instruments; (b) group reading; (c) role-play; and (d) video-recorded interviews. In each center, at least one researcher who is not involved in the administration of the interventions will be trained in the use of assessment tools and inter-rater reliability.

## 6. Ethical Issues

This study will be carried out in accordance with globally accepted standards of good practice and in agreement with the Declaration of Helsinki and with local regulations. The study investigators will ensure that all mental health professionals involved in the study are qualified and informed about the protocol, interventions, and trial-related duties.

A formal ethical approval has been obtained by the Coordinating Center’s Ethics Committee (approval number: prot. 0032758/i). Each participating center will submit the approval to their local ethics committees.

## 7. Assessment Time and Instruments

The following activities are planned for the first three months of the study: (1) the obtaining of approval from local ethics committees; (2) the training of mental health professionals in the interventions and in the use of evaluation tools; and (3) the implementation of the interventions. The recruitment of the patients and their relatives will take place between month 4 and month 12. The patients will be randomly assigned by the coordinating center only after the receipt of written informed consent. The implementation of the intervention will take place between month 3 and month 18. Assessments will be performed between month 3 and month 36. The timeline of the study is shown in Table 1.

The socio-demographic and clinical characteristics of the patients and their relatives will be collected at baseline through validated assessment instruments (Table 2). Researchers participating in the study will be blinded to patient allocation. All patients will be assessed at the following time points: baseline (T0); 6 months post-randomization (T1); 12 months post-randomization (T2); and 24 months post-randomization (T3). All data will be collected during paper and pencil interviews. Each assessment is expected to take about 90/120 min per patient and 60/90 min per relative. During the evaluation, if the participant feel distressed or exhausted, the assessment can be stopped and another appointment can be scheduled for the following 2/3 days.

## 8. Anticipated Results

### 8.1. Primary Outcomes

We expect that, at the end of the intervention, the MDD patients in the experimental group will show a significant reduction in the severity of their depressive symptoms compared with those in the control group. Moreover, we also expect the treated patients to report an improvement in their functioning and an increase in their social network at six months (i.e., improvements in the number of weekly social contacts, practical and emotional support from their social network, and an improvement in the quality of their intimate supportive relationships). We expect that these results will be maintained after 12 and 24 months, albeit with a reduction in magnitude.

### 8.2. Secondary Outcomes

We expect that, compared with those in the control group, the patients receiving the PFI will report a significantly lower number of relapses and hospitalizations after 12 and 24 months as well as improvements in their adherence to pharmacological treatments, quality of life (evaluated using the Manchester Short Assessment of Quality of Life), and coping strategies, and a reduction in their internalized stigma. With respect to coping strategies, we expect an increase in the relatives’ problem-oriented coping strategies (i.e., maintenance of social interests, involving the patient in social activities, positive communication with the patient, seeking information, talking with friends and/or relatives about the patient’s situation) and a reduction in emotion-focused coping strategies (i.e., collusion, avoidance, resignation, coercion, use of alcohol and/or drugs). Moreover, we expect reductions in objective and subjective family burden and improvements in expressed emotions and quality of life, both at the end of the intervention and at follow-ups.

### 8.3. Exploratory Outcomes

The presence of childhood traumas and certain affective temperaments (i.e., cyclothymic, irritable, and hyperthymic temperaments) can be considered possible predictors and/or mediators of response to psychosocial treatments. Thus, these risk factors will be included as possible moderators in order to assess the influence of these variables on the efficacy of the experimental intervention. Additionally, a series of clinical indicators of illness severity will be collected (including age at onset of the first episode, previous psychiatric hospitalizations, number and type of suicide attempts, alcohol and drug use, presence of psychotic symptoms during acute phases, severity of symptoms at baseline, and adherence to pharmacological treatments), and these will be used as explanative variables. Multivariable models will be corrected for these variables in order to identify patients who are more likely to be responsive to the effects of PFIs.

## 9. Statistical Analyses

### 9.1. Power Analysis

The sample size was estimated with respect to the measurement of the main outcomes of the study, and the measure that required the largest sample size (HAM-D) was taken as the reference. Specifically, a sample size sufficient to reduce the total HAM-D score by 10%, with a two-tailed probability of 0.05% and a power of 90%, was estimated. The multicenter design of the study required an adjustment of the sample size estimate in accordance with the value of the intracluster correlation coefficient, set at 0.030, and the coefficient of variation of cluster sizes, set at 0.400. The estimated sample size is 176 patients, 88 for each arm. Based on previous studies conducted with similar patient populations, a dropout rate of 15% is expected. Therefore, it will be necessary to recruit 384 families, 192 for each arm. Each participating center is expected to recruit 16 families (8 for each arm).

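### Section 9.1 adjusts the sample size for centre clustering although patients are randomised individually within centre, and 176 patients with 15% dropout do not lead to 384

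*Protocol article*

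**What the plan says.** Section 9.1 bases the sample size on a 10% reduction in the HAM-D total, with 90% power and a two-tailed probability printed as 0.05%. It continues: "The multicenter design of the study required an adjustment of the sample size estimate in accordance with the value of the intracluster correlation coefficient". The value taken for this ICC is 0.030, and it is combined with "the coefficient of variation of cluster sizes, set at 0.400". The result is 176 patients (88 per arm). With an expected dropout of 15%, the section then concludes that 384 families (192 per arm) must be recruited, 16 per centre and 8 per arm in each.

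Section 3 describes the allocation: "Patients will be randomly assigned in a 1:1 ratio to the experimental group or the control group", and "The randomization will be stratified according to the recruiting center and each patient’s age, sex, and educational level". There are 24 centres. Section 4 adds: "The experimental intervention will be administered individually to each recruited family".

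The GEE covariates listed in Section 9.2 include age, gender and several clinical variables, but not centre.

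**The concern.** An ICC combined with a coefficient of variation (CV) of cluster size belongs to a design in which whole clusters are allocated to one arm. In this trial every centre contributes to both arms, so what patients in a centre share is common to the two groups being compared. The reason given for the adjustment, the multicentre design, does not call for an upward correction.

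In addition, the step from 176 to 384 is presented as a consequence of 15% dropout, and the arithmetic does not bear that out.

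Section 9.1 is the article's only justification of the trial's size. As it stands, a reader cannot learn from it what effect the trial can detect.

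**Working it through.** **Inputs.** From Section 9.1: ICC 0.030, CV 0.400, N 176 (88 per arm), dropout 15%, target 384 (192 per arm), 16 families per centre, power 90%. From Section 3: 24 centres and individual 1:1 allocation stratified by centre. Assumption: two-sided alpha of 5%, taking the printed 0.05% as a slip.

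**1. Can 176 be reproduced?** No. A 10% reduction needs a HAM-D mean and standard deviation, and neither is given. For illustration, assumed baseline means of 15 to 25 and SDs of 3 to 7 give unadjusted totals from 62 to 916. The formula, the cluster size and the N before adjustment are not printed either.

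**2. Factor implied by the stated inputs, if whole centres were allocated.** DE = 1 + ((1 + CV²)m − 1) × ICC.
- m = 8: 1 + (1.16 × 8 − 1) × 0.03 = 1.248
- m = 16: 1 + (1.16 × 16 − 1) × 0.03 = 1.527

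**3. Factor for the design described.** Split the outcome variance into a centre part (ICC) and a within-centre part (1 − ICC). With 8 and 8 per centre, the centre part enters both arm means equally and cancels from their difference. The factor is 1 − 0.03 = 0.97 when centre is in the model. A simulation of 24 centres of 8 and 8 with this ICC gave 0.969. If the analysis ignores centre, the factor is about 1.00. The CV of centre size plays no role.

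**4. From 176 to 384.**
- Dropout only: 176 / 0.85 = 207.1, so 208 with equal arms.
- Design effect applied after 176, m = 8: 176 × 1.248 / 0.85, so 259.
- Design effect applied after 176, m = 16: 176 × 1.527 / 0.85, so 317.
- Multiplying by 1.15 instead of dividing by 0.85 gives smaller totals: 203, 253 and 310.
- To reach 384, the design effect would have to be 384 × 0.85 / 176 = 1.85, which needs m of about 25. Alternatively, dropout would have to be 1 − 176/384 = 54%.
- 24 centres × 16 families = 384 exactly.

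**5. Direction of the clustering error.** If 176 already contains the factor, the N without it is 176 / 1.248 = 141 (m = 8) or 176 / 1.527 = 115 (m = 16). Power with 88 per arm under the actual design would then be about 95–96% or 98%, above the stated 90%.

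**6. What 384 can detect.** d = (1.960 + 1.282) × √(2/n per arm), at 90% power.
- 192 per arm (all 384 analysed): 0.33
- 163 per arm (384 × 0.85 ≈ 326): 0.36, or 0.354 with the factor 0.97
- 88 per arm with no inflation, for comparison: 0.49

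With alpha taken literally as 0.05%, the first two become 0.49 and 0.53.

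**The case against.** The strongest defence is that the ICC may not describe centres at all. Section 5 says "Two mental health professionals per center (at least one being a psychiatrist) will participate in a four-day training course", so families in the same arm and centre share a small number of therapists. An ICC for therapist or centre-by-arm clusters, with a mean size and a CV, is a legitimate inflation even under individual randomisation. At 8 families per cluster it would be about 1.25. This stands as a possibility. However, Section 9.1 gives the multicentre design as its reason and mentions neither therapists nor variation of the treatment effect between centres. Even this reading leads to about 259 patients, not 384.

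A second defence is that a journal article may leave the formula to the full protocol. That is fair, and the missing formula is not the complaint. The printed reason and the printed figures are.

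A reader might also go further than the text allows in four ways:
- *The plan certainly used the cluster-randomised formula, so its standard error is too large by some definite percentage.* The inputs point strongly to that formula, but no formula, cluster size or standard error is printed, so the inflation inside 176 cannot be measured.
- *Clustering explains the gap between 176 and 384.* No version tried does so.
- *Because of clustering, the trial detects about 0.35 rather than 0.49.* Nearly all of that change comes from having 163 instead of 88 per arm. The clustering factor only moves 0.359 to 0.354. Moreover, 0.49 applies only if 176 contains no inflation. If it does, the implied difference is about 0.55 (m = 8) or 0.60 (m = 16).
- *The trial is underpowered.* The error runs the other way.

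**Conclusion.** The point holds in two parts of unequal weight.

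The lesser part is that the reason given for the ICC and CV adjustment does not fit individual randomisation stratified by centre. The appropriate factor for a shared centre effect is about 0.97, or 1.00 at most, rather than about 1.25 to 1.53. This is conservative, introduces no bias, and is of unverifiable size within 176.

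The weightier part is that 176, 15% and 384 are mutually inconsistent. The stated route gives 208, and the most generous reading tried gives about 317. That 384 equals 24 × 16 suggests that it may reflect the number of centres and their quotas, but the document does not say so.

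The factor 0.97 assumes near-equal arms within each centre and centre in the model. The detectable differences of 0.33 to 0.36 assume two-sided 5% alpha and a simple comparison of two means. The lower value applies if all 384 are analysed, as intention-to-treat with LOCF in Section 9.2 would suggest, and the higher if about 326 complete.

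**What to change.** Rewrite Section 9.1 for individual randomisation stratified by centre:
- Drop the ICC and CV inflation. If therapist or centre-by-arm clustering was meant, name it and give its ICC and cluster size.
- State the HAM-D SD (and the mean to which the 10% refers) and the N before any adjustment.
- Reconcile 176, 15% and 384. If 384 was set by 24 centres recruiting 16 families each, say so.
- Correct the printed alpha if 5% was intended.
- Report the difference detectable with 90% power for the planned 384, in standard deviations and in HAM-D points: about 0.33 SD if all are analysed, about 0.36 SD with about 326 completers.

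In Section 9.2, add centre to the GEE model, since it is a stratification factor.

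The cost is one rewritten paragraph and one additional factor in the model. No extra patients are needed and enrolment need not change.
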